# Impact of non-restorative cavity control on proximal carious lesions of anterior primary teeth on the tooth survival and patient-centered outcomes (CEPECO 2): study protocol for a non-inferiority randomized clinical trial

**DOI:** 10.1186/s12903-021-01524-0

**Published:** 2021-03-31

**Keywords:** Dental caries, Non-restorative treatment, Resin composite, Deciduous teeth

## Abstract

**Background:**

Studies have questioned the necessity of restoring cavitated carious lesion on primary teeth, once the control of biofilm is the most important factor to arrest these lesions. This randomized clinical trial aimed to compare the survival of teeth treated with a non-restorative cavity control (NRCC) compared to resin composite restorations (RCR) on proximal carious lesion in anterior primary teeth, as well as the impact of these treatments on patient-centered outcomes.

**Methods:**

A randomized clinical trial with two parallels arms (1:1) will be conducted. Children between 3 and 6 years old will be selected from the Center of Clinic Research of Pediatric Dentistry of Ibirapuera University (UNIB), a dental trailer (FOUSP) located on Educational Complex [name] de Lima, the Pediatric Dentistry Clinic of Santa Cecília University and from the Pediatric Dentistry Clinic of University Center UNINOVAFAPI. One hundred and forty-eight teeth will be randomly distributed in two experimental groups: (1) Selective removal of carious tissue and RCR; or (2) NRCC through cavity enlargement using a metallic sandpaper. The primary outcome will be tooth survival after 6, 12, 18 and 24 months. The duration and the cost of dental treatments will be considered for the estimation of the cost-effectiveness of the evaluated treatments. The discomfort reported by the participants will be measured after each treatment using the FIS scale. The participants’ satisfaction and perception of the parents/legal guardians will be evaluated through questionnaires. For the primary outcome, Kaplan–Meier’s survival and Long-Rank test will be used for comparison between the two groups. All the variables will be modeled by Cox regression with shared fragility. Significance will be considered at 5%.

**Discussion:**

The NRCC could be an option to manage carious lesions on proximal surfaces of primary teeth, and the approach could be well accepted by the children and parents/legal guardians.

*Trial registration* Clinicaltrials.gov registration: NCT03785730, Registered on December 18th 2018, first participant recruited 30/04/2019, https://clinicaltrials.gov/ct2/show/NCT03785730.

Ethics Reference No: 91569118.8.0000.5597.

Trial Sponsor: Universidade Ibirapuera.

The Trial was prospectively registered.

## Background

Despite the reduction in the prevalence of dental caries, especially in Pediatric Dentistry, caries is still considered a public health problem, since it affects more than 50% of pre-school and school-age children [1]. Data from previous studies also suggest that around 10 to 50% of these children have cavitated lesions on anterior teeth [2–4], which results in negative impact on their quality of life [4]. The evolution of the disease leads to loss of self-esteem, masticatory difficulty, pain, and frustration [4].

Thus, treatments that prevent the progression of these lesions and allow the maintenance of primary teeth until exfoliation while improving the patient's quality of life should be investigated. Restorative techniques are a treatment option for such cavitated lesions [5], but although the available restorative materials have improved, restorations often need replacement, mainly due the patient's failure to control caries risk factors [6].

Since biofilm control is the most critical factor for lesion arrestment, the approach of restoring primary teeth has been questioned [7]. This is corroborated by studies that show that a large part of primary teeth with untreated carious lesions exfoliate without showing any symptoms [8–10].

Therefore, the non-restorative cavity control (NRCC) has been suggested as an option for the treatment of carious lesions in primary teeth. This approach consists of an enlargement of the cavity to allow the adequate removal or disorganization of the daily biofilm through toothbrushing [11–13].

Studies found that this approach shows similar results regarding the improvement of oral-health-related quality of life after one year of treatment [12] and teeth longevity after 3.5 years of follow up [13] compared to conventional composite resin restoration and atraumatic restorative treatment. However, these data come from studies based on posterior teeth restorations [11–13]. Aesthetic is one of the main reasons for replacing restorations in anterior teeth [6], favoring patient engagement for oral care, could also be a stimulus for a frequent brushing of teeth treated with NRCC. However, the acceptability and longevity of this approach has not been compared with the conventional treatment.

This study aims to evaluate the impact of NRCC for proximal carious lesions in anterior primary teeth on teeth survival. The secondary outcomes will be cost-effectiveness and patients-centered outcomes between the two treatment options. We hypothesize that the survival of teeth treated with NRCC is non-inferior, with a non-inferiority margin of 15%, from that of teeth restored with composite resin.

## Methods/design

### Study design and ethical aspects

This non-inferiority randomized controlled clinical trial, with two parallel groups with 1:1 allocation ratio was reported according to the Standard Protocol Items for Clinical Trials (SPIRIT) and then registered on the ClinicalTrials.gov platform (NCT03785730). The protocol was approved by the Research Ethics Committee of Universidade Ibirapuera (UNIB). The other centers involved are considered co-participants (Centro Universitário do Norte—Uninorte, Centro Universitário Uninovafapi—UNINOVAFAPI, and School of Dentistry from the University of Sao Paulo—FOUSP).

Children aged 3 to 6 years with at least one proximal cavitated lesion on anterior primary teeth will be selected. Teeth will be randomly allocated to selective removal of carious tissue and resin composite restoration (RCR) or NRCC. Tooth survival after two years of follow-up will be the primary outcome and cost-effectiveness, satisfaction, and discomfort reported by participants and parents/guardians’ perception will be the secondary outcomes.

Only patients who fulfill the eligibility criteria will be included in the study after the legal guardians sign the informed consent form and the child consents to participate in the study.

### Sample selection

For sample size calculation, we used an expected survival of primary teeth with cavitated lesions in dentin affecting the proximal surface submitted to NRCC of 89.7% after 24 months [13] and a clinically significant difference of 15% in the success rate between groups. Considering a non-inferiority study, a significance level of 0.05 and a power of 0.80, we reached the final number of 102 teeth. Since each child can contribute with more than one tooth, 20% was added to this value (cluster per child), and 20% more was added due to possible sample losses. Thus, the final rounded number of 74 teeth per group was reached, resulting in a total of 148 teeth (sealedenvelope.com).

Children aged 3 to 6 years will be selected from the Clinical Pediatric Research Center—UNIB (CEPECO) (São Paulo, SP, BR), Pediatric Dentistry Clinic—Uninorte (Manaus, AM, BR), Pediatric Dentistry Clinic—UNINOVAFAPI (Teresina, PI, BR) and dental trailer (FOUSP) located on Educational Complex [name] de Lima (Barueri, SP, BR). The screening will be carried out under natural light with the aid of a wooden spatula. Potentially eligible children will be referred for clinical examination.

Recruitment will be taking place from April 2019 to December 2021. After allocation and treatment, the children will be followed up for 24 months. Table 1 displays the flow diagram of the clinical trial phases.

**Table 1 Tab1:** Flow diagram of clinical trial’s phases in according to SPIRIT

Timepoint**	Study period						
	Enrolment	Allocation	Post-allocation				Close-out
	*−t*_*1*_	0	*t*_*1*_	*t*_*2(6 m)*_	*t*_*3(12 m)*_	*t*_*4(18 m)*_	*t*_*5(24 m)*_
*Enrolment*							
Eligibility screen	X						
Informed consent	X						
Allocation		X					
*Interventions*							
NRCC			X				
RCR			X				
*Assessments*							
Survival of tooth				X	X	X	X
Cost-effectiveness			X				X
Discomfort reported by participant			X				
Satisfaction of the participants				X			
Perception of the Parents/legal Guardians		X	X	X			

### Clinical examination

Initially, a clinical exam will be carried out in a dental office by the operators using a light reflector, mirror, and WHO probe, after prophylaxis to identify the eligible participants.

### Eligibility criteria

Children that present at least one cavitated carious lesion on the proximal surface of anterior teeth will be included.

Patients with special needs, who use orthodontic braces, and/or present systemic diseases that could influence the oral cavity will be excluded. Additionally, teeth with carious lesion that affect more than one third of the buccal and/or lingual surfaces, with previous history of dental trauma, pulp exposure, spontaneous pain, pathological mobility, abscess or fistula, teeth with restorations, developmental enamel defects or physiological mobility (exfoliation) will be excluded.

### Operator’s training

Four pediatric dentists will be trained to perform the two techniques (NRCC and resin composite restorations—RCR). The training will consist of theoretical classes and laboratory activities for three hours each.

### Sequence generation

Teeth will be randomly assigned into one of the groups considering the strata of the research center (UNIB, FOUSP, Uninorte, and UNINOVAFAPI), in 4, 6, and 8 blocks, according to the sequence obtained by an external examiner generated by the website www.sealedenvelope.com.

### Allocation concealment mechanism

The generated sequence will be distributed in sequentially numbered opaque sealed envelopes by an external researcher, and the envelopes will be opened by the dental assistant immediately before the treatment.

### Interventions

For teeth of the RCR Group, after prophylaxis and cotton roll isolation, selective removal of carious tissue will be performed, removing infected dentin from the pulp wall and with total removal of carious tissue of the surrounding walls, using curettes compatible with cavity size. The acid conditioning will be performed only in enamel for 15 s with 37% phosphoric acid gel. The adhesive system will then be actively applied for 20 s in both enamel and dentin, followed by air-drying for 5 s and light-curing for 10 s (Single Bond Universal; 3M/ESPE, St. Paul, USA). Resin composite (Z250, color B1; 3M/ESPE, St. Paul, USA) will then be placed in the cavity with the aid of a spatula of insertion and polyester matrix. Before finishing and polishing, the occlusion will be checked with carbon paper and adjusted if necessary.

For teeth randomized to NRCC Group, the proximal cavities will not be restored, but enlarged with metallic sandpaper, exposing the cavity, to allow access for toothbrushing associated with 1000 ppm fluoride toothpaste [13] (Fig. 1).

**Fig. 1 Fig1:**
[figure not shown]
Illustration of NRCC treatment. Dashed lines represent the cavity’s size limit to be included in the study (up to one-third of the buccal and/or lingual surfaces involved in the proximal carious lesion). In the first image, we can observe a proximal carious lesion in the upper incisor. This cavity will be enlarged with metallic sandpaper in the buccal and lingual direction, exposing the cavity, as demonstrated in the second image

All participants and their respective guardians will receive hygiene and diet instructions in the first clinical appointment and at every follow-up. Other teeth with carious lesions not included in the research will be treated according to the diagnosis. The toothbrushes and toothpaste will be also provided to the participants.

The risks for participants will be minimal and related to carious lesion progression. No adverse effect of the interventions is expected. To guarantee participant adherence to the study, social media will be used and participants will be contacted by mobile message applications.

### Blinding

Blinding of operators, participants, and examiners will not be possible due to the evident differences between the interventions. However, an external researcher not directly involved in the study will perform the statistical analysis of the data.

### Data collection and evaluated outcomes

All data obtained will be tabulated by a researcher and checked by another researcher. An identifying number will ensure participants' confidentiality. The data will be stored on the cloud with access restricted to the researchers involved in the project and the principal investigator. After completing the study and data deidentification, the data will be used in an open electronic database to ensure research transparency. Due to the short follow-up, there will be no data monitoring committee. However, the coordinator of the trial will be responsible for periodical auditing.

The explanatory variables—sex, age, toothbrushing, use of fluoride toothpaste, and dental floss—will be collected by a questionnaire with closed-ended questions. Tooth survival after two years of follow-up will be considered as the primary outcome. Secondary outcomes will be the cost-effectiveness of both treatments, satisfaction, and discomfort reported by participants and parents/guardians' perception.

Patients will be contacted by telephone for recall of the periodical appointments. For those who cannot be contacted after several phone call attempts, a letter will be sent to the home address.

Four examiners will be trained for the assessed outcomes in two stages:Theoretical classes with images (three hours).Clinical setting with children with similar conditions to the eligible ones, but not included in the study (three hours).

### Primary outcome

#### Tooth survival

Survival of the tooth will be evaluated at 6, 12, 18, and 24 months after the initial intervention through clinical examination. A successful treatment will be considered when the teeth is without clinical signs or symptoms of pulp pathology or exfoliated, with no need for more invasive interventions, such as pulpectomy or extraction.

In cases of failed RCR, no further treatment will be performed, and the tooth will continue to be monitored for up to 24 months. If patients report pain or present the need for more invasive interventions, the necessary treatment will be performed.

### Secondaries outcomes

#### Cost-effectiveness

An economic cost-effectiveness analysis will be carried out considering the payer perspective (Unified Health System) and tooth survival as treatment effectiveness. The direct costs for the procedures performed in each of the two groups will be measured and evaluated, as well as the labor cost of the professionals involved in the clinical attendance (direct costs). The costs of all the materials used will be computed using the average market value in different dental material stores, and these data will be updated during the study. The labor costs will be measured by the time required to perform the treatment. The time required to perform the procedure will be measured with a stopwatch. Time will start right after the prophylaxis for both groups and will be stop after the finalization of the intervention. The average time will be calculated for each group. Patient costs with transportation and time will not be analyzed (indirect costs).

Thus, the incremental cost-effectiveness ratio (ICER) will be calculated considering a rate between the total cost of each treatment and tooth survival rate after two years, according to the following formula:$$ICER=\left[\frac{Cost\; of\; intervention\; RCR}{Survival\;\; of\; intervantion\; RCR}\right]-\left[\frac{Cost\; of\; intervention\; NRCC}{Survival\; of\; intervention \; NRCC}\right]$$

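### The cost rules most naturally cover only the allocated procedure, while effectiveness runs to 24 months; no stated rule collects or adds the cost of treating teeth that fail

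*Protocol article*

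**What the plan says.** All references are to the protocol article.

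Under Cost-effectiveness, the analysis is done "considering the payer perspective (Unified Health System) and tooth survival as treatment effectiveness". On cost items it says: "The direct costs for the procedures performed in each of the two groups will be measured and evaluated". On labour: "The labor costs will be measured by the time required to perform the treatment". The stopwatch rule is: "Time will start right after the prophylaxis for both groups and will be stop after the finalization of the intervention". The time is then averaged within each group. Materials are priced at average market value, updated during the study. The only stated exclusion is "Patient costs with transportation and time will not be analyzed (indirect costs)".

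The summary measure is described as "a rate between the total cost of each treatment and tooth survival rate after two years". The displayed formula is the cost of the RCR intervention divided by its survival, minus the same ratio for NRCC.

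Under Tooth survival, success requires a tooth "with no need for more invasive interventions, such as pulpectomy or extraction". A failed restoration by itself is only monitored. Beyond that: "If patients report pain or present the need for more invasive interventions, the necessary treatment will be performed".

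Table 1 marks cost-effectiveness at the treatment visit and at 24 months, but not at 6, 12 or 18 months.

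**The concern.** Cost and effect seem to be measured over different periods. A tooth that fails at, say, 12 months lowers its arm's survival. The pulpectomy or extraction that follows is a direct cost to the same payer inside the same 24 months, but the stated rules do not bring it into the numerator. The stopwatch covers labour time only. For later materials and procedures, the gap rests on the wording of the formula and on the lack of any rule for collecting them.

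The direction is predictable. Leaving out treatment after failure helps whichever arm fails more. The Discussion expects NRCC to have shorter chair-time and lower cost. If NRCC also had the lower survival, its economic advantage would be overstated in just the situation where a payer most needs the full cost.

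**Working it through.** **The plan's own figures.** The cost-effectiveness section states no number. The sample-size figures, used here for the failure counts, reproduce. With 89.7% survival in both arms, a 15-point margin, one-sided alpha 0.05 and power 0.80, the requirement is 51 teeth per arm, 102 in all. Then 102 x 1.2 x 1.2 = 146.9, rounded up to 74 per arm, 148 in all.

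**Teeth that could need treatment after failure (74 per arm).**
- Planning rate: 74 x (1 - 0.897) = 7.6 per arm, so about 15 over both arms.
- NRCC at the margin (89.7% - 15 points = 74.7%): 74 x (1 - 0.747) = 18.7, so 7.6 + 18.7 = about 26 over both arms.

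These are upper figures. They assume that no teeth are lost and that each failed tooth has one re-treatment.

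**Effect on the protocol's measure.** The article gives no unit costs, so the following are assumptions. The first-visit cost of RCR is 1, that of NRCC is c, and each failed tooth in either arm costs R more. With survival S_R (RCR) and S_N (NRCC):

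- First-visit costs only: 1/S_R - c/S_N
- Costs to 24 months: [1 + R(1 - S_R)]/S_R - [c + R(1 - S_N)]/S_N

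A positive value favours NRCC. Worked example with c = 0.5, S_R = 0.897, S_N = 0.747:
- R = 0: 1/0.897 - 0.5/0.747 = +0.445
- R = 1: 1.103/0.897 - 0.753/0.747 = +0.222
- R = 2: 1.206/0.897 - 1.006/0.747 = -0.002

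Other NRCC survival values, RCR at 89.7% and c = 0.5:

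| NRCC survival | R = 0 | R = 1 | R = 2 | R = 3 |
|---|---|---|---|---|
| 89.7% | 0.557 | 0.557 | 0.557 | 0.557 |
| 82% | 0.505 | 0.400 | 0.296 | 0.191 |
| 74.7% | 0.445 | 0.222 | -0.002 | -0.226 |

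The value of R at which the sign changes depends heavily on c:

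| NRCC survival | c = 0.3 | c = 0.5 | c = 0.8 |
|---|---|---|---|
| 82% | about 7.2 | about 4.8 | about 1.3 |
| 74.7% | about 3.2 | about 2.0 | about 0.2 |

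These apply to the protocol's difference of cost-to-survival ratios. In plain cost per tooth, with c = 0.5 and NRCC at 74.7%, NRCC stays cheaper until R = 0.5/0.15 = 3.3.

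**The case against.** A reader might infer that the plan excludes the cost of pulpectomies and extractions, or that the stopwatch rule makes later treatment impossible to cost. The document supports neither. The only exclusion is patient transport and time. The references to procedures performed in each group, to all materials used and to the total cost of each treatment can be read to include later care, and so can the 24-month mark in Table 1. That mark may, however, reflect only the survival input. The article also uses the word intervention for pulpectomy and extraction, so it is not strictly confined to the first procedure. A rule for timing one procedure does not forbid timing another. All of this stands.

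A journal article condenses, and a fuller document may hold the collection rules. This stands in part. But the article itself fixes the perspective, the start and stop of the clock, the averaging and the formula, and taken as written these do not reach the treatment that its own outcome section foresees.

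A failed restoration alone receives no further treatment, so repair or replacement adds no cost. That is right, and it narrows what is at stake. The counts above are failed teeth, not failed restorations.

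Finally, survival in the denominator already penalises the arm that fails more, and the largest shifts need a deficit near the margin, where non-inferiority would be unlikely to be shown. Both are fair. The penalty is partial, and at 82% survival the shift is smaller but not nil.

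**Conclusion.** The point holds as a gap between the cost rules and the stated perspective and time horizon, not as a stated exclusion of re-treatment costs. Followed literally, the rules count the allocated procedure and leave out payer costs after failure.

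The size cannot be fixed from the document. In the assumed case at the margin with c = 0.5, the measure roughly halves when a re-treatment costs one RCR and reaches about zero when it costs two. With equal survival and equal re-treatment cost, which includes the survival assumption that reproduces the sample size, the effect is nil. The results rest on assumed cost ratios, the same R in both arms and one re-treatment per failed tooth. Only a secondary outcome is affected; the primary analysis is not touched.

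**What to change.** Define cost per tooth as the allocated procedure plus every payer-side procedure on the study tooth up to 24 months. Record time and materials for each later procedure in the same way as for the first, and use the mean 24-month cost per arm in the analysis. If a first-visit scope is intended, say so openly and limit the conclusion to it.

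The cost is a few lines of wording and a log of about 15 to 26 events if every failure is treated and no teeth are lost. The drawbacks are a little extra data collection and retrospective costing of any re-treatment already done. Clinical care does not change.

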### Data analysis

The efficacy of each treatment will be evaluated according to five main outcomes:Tooth survival (primary outcome): The outcome will be dichotomized as survival versus failure. Kaplan Meier’s plot with overall survival in intention-to-treat (ITT) study population will be performed. The ITT study population will include all randomized participants regardless of protocol deviations, non‐compliance, or early study withdrawal. The Log-Rank test will be used to compare the survival curves of the two groups. The multivariate Cox regression with shared frailty model will be used to evaluate the influence of the explanatory variables (sex, age, jaw, type of teeth, toothbrushing, use of fluoride toothpaste, and dental floss) on the outcome. Hazard ratios (HR) with the respective 95% confidence interval will be calculated.Cost-effectiveness (secondary outcome): Incremental cost-effectiveness ratio will be calculated considering the ratio between the total cost of each treatment and tooth survival after two years.Discomfort reported by the participants (secondary outcome): The data will be summarized as the mean with the standard deviation or the median with the interquartile range, as appropriate. The two groups will be compared after confirming the distribution of data (Normal/non-normal), using the Student's t-test or Mann–Whitney test.Satisfaction of the participants (secondary outcome): The data will be summarized as the mean with the standard deviation or the median with the interquartile range, as appropriate. The two groups will be compared after confirming the distribution of data (Normal/non-normal), using the Student's t-test or Mann–Whitney test.Perception of the Parents/Legal Guardians (secondary outcome): The data will be summarized as the frequencies. The two groups will be compared using the Chi-Square Test.

For all analyzes, the significance value will be set at 5%.

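### The quantity that the protocol calls an ICER is a difference of two average cost-per-surviving-tooth ratios, not an incremental cost-effectiveness ratio

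*Protocol article*

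**What the plan says.** The Cost-effectiveness section describes an analysis "considering the payer perspective (Unified Health System) and tooth survival as treatment effectiveness". It then states that "the incremental cost-effectiveness ratio (ICER) will be calculated considering a rate between the total cost of each treatment and tooth survival rate" at two years, and displays the formula:

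ICER = [Cost RCR / Survival RCR] - [Cost NRCC / Survival NRCC]

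The Data analysis section gives the same definition in words: "Incremental cost-effectiveness ratio will be calculated considering the ratio between the total cost of each treatment and tooth survival after two years". Nowhere does the article divide a difference in cost by a difference in survival.

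Two design figures bear on the illustration. Sample selection expects survival of primary teeth "submitted to NRCC of 89.7% after 24 months", and the end of the Background sets the non-inferiority margin at 15%. No cost figures are given.

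**The concern.** An ICER answers one question: what does the payer pay for each additional tooth that survives because the dearer treatment was chosen? It needs the cost difference in the numerator and the survival difference in the denominator. The displayed formula instead works out an average cost per surviving tooth in each arm and subtracts one from the other.

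The formula and two verbal statements agree with each other, so this is neither a typing slip nor a fault of text extraction. It is also not a detail left to a fuller document, because the article commits to a specific expression.

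At stake is a named secondary outcome. A payer who sees a figure labelled ICER will compare it with what an extra surviving tooth is worth, and this figure does not support that comparison. The Discussion expects NRCC to cost less, so the cost-effectiveness result is likely to be used in the argument for adopting it.

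**Working it through.** **Inputs.** From the protocol: NRCC survival 0.897 at 24 months and a margin of 0.15. Assumed: all costs, in arbitrary units, and the remaining survival values. The protocol states no ICER value, so there is none to reproduce.

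**What the design assumes about survival.** The stated 102 teeth can be reproduced with equal survival of 0.897 in both arms, one-sided 0.05 and power 0.80:

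n per arm = (1.645 + 0.842)² × 2 × 0.897 × 0.103 / 0.15² = 50.8, rounded up to 51, or 102 in total.

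The sample size is therefore consistent with a planned survival difference of zero, which matters for the fix.

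**Formulas compared** (C = mean cost, S = 24-month survival; R = RCR, N = NRCC):

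- Plan: C_R/S_R - C_N/S_N
- ICER: (C_R - C_N)/(S_R - S_N)

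**Assumed costs 60 (RCR) and 20 (NRCC):**

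| S_R | S_N | Plan | ICER |
|---|---|---|---|
| 0.897 | 0.747 | 66.89 - 26.77 = 40.1 | 40/0.150 = 267 |
| 0.900 | 0.897 | 66.67 - 22.30 = 44.4 | 40/0.003 = 13,333 |
| 0.897 | 0.930 | 66.89 - 21.51 = 45.4 | 40/(-0.033) = -1,212 (NRCC cheaper and better) |

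In the first row NRCC loses 15 points against an RCR survival of 0.897.

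**Other assumed cost pairs, S_R = 0.947 and S_N = 0.897:**

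| C_R | C_N | Plan | ICER |
|---|---|---|---|
| 100 | 50 | 49.86 | 1,000 |
| 100 | 80 | 16.41 | 400 |
| 60 | 50 | 7.62 | 200 |

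**Sign.** The plan's value is positive when C_R/C_N exceeds S_R/S_N, and negative when it is smaller. Take costs 55 and 50 with survival 0.95 and 0.80. The cost ratio is 1.10 and the survival ratio is 1.19.

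- Plan: 55/0.95 - 50/0.80 = 57.89 - 62.50 = -4.6
- ICER: 5/0.15 = +33.3 per additional surviving tooth

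**Effect on a decision.** In the first row of the first table, suppose a payer values an additional surviving tooth at 100 (assumed). The net benefit of RCR is 100 × 0.15 - 40 = -25, so RCR is not worth its extra cost. A reported ICER of 40.1 lies below 100 and would suggest that it is. In the third row, 45.4 read as an ICER would suggest that RCR buys extra teeth, when in that row it costs more and saves fewer.

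**The case against.** The best defence is that the printed quantity can be computed and has a meaning: it is the difference between the arms in average cost per surviving tooth. It also moves in a sensible direction, since in the first table it rises as NRCC survival improves relative to RCR. That stands. The faults are the name, the quantity being estimated and the number reported under that name. The expression is not meaningless.

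A second defence is that the standard ICER behaves badly here. The 13,333 above comes from a denominator of 0.003, and with equal survival the ratio is undefined. That also stands. It argues for reporting more than the ratio, but it does not make the printed formula an ICER.

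Two stronger readings are tempting, and the documents do not support them.

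- A reader might infer that the formula always flatters the cheaper arm. It does not. The direction depends on the cost ratio relative to the survival ratio, and the 55 against 50 example gives a value that favours the dearer arm. The protocol gives no costs from which to tell which case will apply.
- A reader might infer that the costs of treating teeth that fail during follow-up are left out. The stopwatch timing does cover only the intervention. But the costing refers to procedures performed in each group and to total cost, and Table 1 marks cost-effectiveness at 24 months as well as at treatment. The Tooth survival section says that a failed restoration is monitored without further treatment unless there is pain or a need for more invasive care. Whether the cost of that later care is counted is left open.

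**Conclusion.** The concern holds. Following the protocol as written would report a difference of two average ratios under the name ICER. The two quantities differ in every case shown, often by a large factor (40.1 against 267; 49.86 against 1,000), and they can differ in sign (-4.6 against +33.3). The sizes rest on assumed costs. That the two formulas are different quantities does not.

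This is a should-fix. It affects one secondary outcome and leaves the primary outcome, sample size and randomisation untouched. The correct quantity can be computed from the cost and survival data that the trial already plans to collect. Whether later treatment costs are included is a separate clarification and not part of the error.

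**What to change.** 1. In the Cost-effectiveness section, replace the displayed formula with ICER = (mean cost RCR - mean cost NRCC) / (24-month survival RCR - 24-month survival NRCC). Change the sentence before it and the matching sentence in Data analysis to agree. If the present quantity is kept as well, call it the difference in average cost per surviving tooth.
2. Report incremental cost and incremental survival separately, each with a confidence interval, because the ratio is unstable or undefined when survival is nearly equal. A child can contribute several teeth, so the intervals should allow for clustering. A bootstrap that resamples children and keeps each child's teeth together is one way. Incremental net benefit over a range of willingness-to-pay values is a convenient summary that avoids the ratio. These are options, and the first step is the correction itself.
3. State whether the cost of treating teeth that fail within 24 months is counted.

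The cost is one formula, two sentences and a modest amount of programming. Steps 1 and 2 need no new data. Step 3 needs extra extraction from clinical records only if those costs are to be counted and are not already being captured.
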